## Abstract

**Introduction:**

The sequelae of moderate-severe acquired brain injury (ABI) encompass motor, cognitive, sensory, emotional and behavioural areas that affect meaningful occupational participation and quality of life, with a high prevalence of associated mental disorders. When the patient returns to community life after discharge from the hospital, specialised care is generally insufficient due to the lack of consideration of the dual condition of mental disorder and ABI. Since there is a negative impact on competence and thus on occupational participation, occupational therapy represents a convenient way of intervention. On these assumptions, a community-based occupational therapy protocol on mental health for people with moderate/severe acquired brain injury (COT-MHABI) is presented. It is focused on meaningful occupational participation and looks for improvement in the quality of life.

**Methods and analysis:**

This study aims: (i) to design a protocol to evaluate the effectiveness of a community occupational therapy intervention based on MOHO for patients with a dual (mental health/ABI) for improving quality of life and self-perceived occupational performance; (ii) to analyse the outcomes of occupational and social variables (occupational balance, participation level, satisfaction with occupation and performed roles and community integration) after the COT-MHABI process; (iii) to analyse the impact of quality of life on satisfaction with occupations performed by this population. A non-randomised controlled clinical trial will be performed. Patients assigned to the experimental group will receive over one year of on-site and telematic occupational therapy sessions, 16 sessions on average. Variables such as quality of life, community integration or satisfaction with occupational performance will be collected at baseline, 6, and 12 months.

**Discussion:**

The needs for the dual mental/ABI population in their reintegration into the community are related to the associated deficits and to the absence of specialised services for the complexity of this patient profile. Few studies consider the coexistence of mental health and ABI issues. The COT-MHABI protocol is proposed to provide continuity to the community needs of this population, conceptualised from occupational participation, person-centred and focused on meaningful activities.

**Clinical trial registration:**

**Trial identifier and registry name** ClinicalTrials.gov ID: NCT04586842
https://clinicaltrials.gov/ct2/show/NCT04586842?term=252136&draw=2&rank=1; Pre-results; Community-based Occupational Therapy Intervention on Mental Health for People With Acquired Brain Injury (COT-MHABI).

## Introduction

Acquired Brain Injury (ABI) constitutes a major health problem throughout the world. It is a leading cause of mortality and a disability producer [1]. In Spain, it is prevalent in over 400,000 people [2]. ABI is defined as a brain injury after birth, resulting from an external force (as in the case of traumatic brain injury) or due to non-traumatic processes (stroke, anoxia, brain tumours, encephalitis, etc.) [3]. The sequelae of moderate-severe ABI encompasses motor, cognitive, sensory, emotional, and behavioural areas that affect occupational participation, social relationships, and the quality of life, often resulting in personality changes [4–12].This population profile shows a significantly high prevalence of associated mental disorders either due to exacerbation of pre-existing symptoms, the onset of organic injury, or the resulting psychosocial situation [13–15].

Thus, people with moderate-severe ABI have, according to the World Health Organization (WHO), a highly complex condition, since it manifests deficits in bodily functions, limits activity, and restricts participation in life situations [16]. WHO itself recognises the importance of the concept of participation by defining it as the act of becoming involved in life situations [17]. Specifically, occupational participation encompasses the performance of meaningful activities that are part of the socio-cultural context. These are influenced by a person’s performance capacity, habits and roles, volitional system (motivation for action), and environmental conditions [18]. Being able to participate in these valuable and meaningful activities has a direct benefit for well-being and life satisfaction [9,11,19].

Likewise, volition decreases, both in terms of control over one’s own life (and, therefore, loss of active agency) [6,8] and in terms of one’s motivation for action [20–22]. Occupational identity, i.e., a person’s perception of himself or herself and who he or she wants to become, and occupational competence, the pattern of participation congruent with that identity [23], are two concepts directly related to role performance [10,18,24], which is also significantly affected [6,25–27].

However, their occupational needs are not adequately covered in the community phase after hospital admission. There are deficiencies such as lack of information, guidance and specialised support, poor quality of care coordination, and scarce resources [2,28–30]. Furthermore, the confluence of previous or subsequent mental disorders interferes with the process of community reintegration, especially with regard to daily performance, because it is difficult to manage both by the person and by his or her social and family environment [13,26,31,32]. The specialised care they receive is generally insufficient because they are treated from a psychiatric or neurological perspective without considering the confluence of both diagnoses simultaneously in treatments and interventions, or they are directly rejected by these services [28,29,33,34], mainly due to lack of knowledge of the relationship between ABI and mental health and the invisibility of many of the associated deficits [31,35,36].

One of the most appropriate disciplines to support survivors in managing the consequences of the deficits produced by ABI is occupational therapy [10]. This is a profession committed to the promotion of health and well-being through occupation, identifying as its main objective the facilitation of people’s participation in activities of daily living [10,37]. In other words, occupational therapy aims to help a person become what he/she wants to become through meaningful action framed within the daily routines and the roles played [18,38].

For this specific population, a person-centred intervention focused on the recovery of meaningful activities and occupations and accompanying the exploration of new and balanced participation options it is recommended [9,12,26]. More specifically, evidence has recommended the use of the Model of Human Occupation (MOHO) in mental health or ABI interventions [10,39–41]. This model, specific to occupational therapy, is the most widely used occupation-focused model in the world [10]. It provides specific assessments and interventions. It is based on four main aspects: motivation for occupation, habits and routines, occupational performance skills, and the influence of the environment on participation [10,23,24].

As shown above, there is evidence for the use of this occupational therapy model in both ABI and mental health populations, but there is a lack of studies and interventions referring to the dual situation of considering mental health issues in patients with ABI.

Due to this lack of evidence, the occupational needs discussed for this complex population and the absence of similar interventions, we present this design for a community-based occupational therapy protocol on mental health for people with moderate/severe acquired brain injury (COT-MHABI).

### Objectives

This study aims: (i) to design a protocol to evaluate the effectiveness of a community occupational therapy intervention based on MOHO for patients with a dual (mental health/ABI) for improving quality of life and self-perceived occupational performance; (ii) to analyse the outcomes of occupational and social variables (occupational balance, participation level, satisfaction with occupation and performed roles and community integration) after the COT-MHABI process; (iii) to analyse the impact of quality of life on satisfaction with occupations performed by this population.

## Materials and methods

### Inclusion and exclusion criteria

The study population (experimental and control group) will be composed of (i) adults aged between 18–50 with (ii) a diagnosis of medium or severe ABI and (iii) a diagnosis of mental disorder following ABI (as recognised in the 5th edition of the Diagnostic and Statistical Manual of Mental Disorders (DSM-5) [42]) presenting behavioural, mood and/or emotional disorder. In addition, (iv) the patient must show difficulties in occupational participation compared with the pre-ABI situation and present occupational needs, as determined by an occupational therapist’s comprehensive assessment plus the patient’s identification of at least two occupational performance problems using the COPM (Canadian Occupational Performance Measure, a more detailed description of the tool in Data collection section of this paper). Patients also must be (v) in a situation of hospital discharge from ABI specialisation units and (vi) domiciled in the same province to which the providing hospital belongs.

Subjects will be excluded if (i) they are in a situation of symptomatological destabilisation with severe functional impairment that, as a priority, requires continued support from specialised mental health units and/or psychiatric or hospital admission, and/or (ii) they were diagnosed prior to the brain injury with a severe mental disorder (e.g., schizophrenia or a major depressive disorder) or dementia, and/or (iii) the cognitive deficits associated with ABI do not allow the agreed establishment of goals autonomously or with minimal support from the main caregiver.

### Recruitment methods

For both the experimental and control groups, the referral of patients to the study will take place through the neuropsychiatry department of the Institut Guttmann Neurorehabilitation Hospital in Badalona (Spain), which does not participate in the al-location of subjects, protocol intervention, data collection, or statistical analysis of the results. This department will assess mental health baseline status using the Neuropsychiatric Inventory Questionnaire (NPI-Q)) [43], evaluating possible interference with the results of concomitant pharmacological treatment.

Regarding the allocation, the experimental group will be composed of patients that will receive the COT-MHABI intervention protocol, framed within a community intervention programme at the hospital, after discharge. As it is a very specific and novel intervention, the resources for its implementation are limited, generating a waiting list (over 12 months). Given that this standby period is longer than the duration of the intervention in the experimental group, patients on the waiting list will be invited to participate in the control group with the consideration of receiving the intervention at a later stage.

### Trial design and setting

Due to the logistical reasons discussed above, a non-randomised controlled clinical trial will be performed. The measurement points of both groups will be comparable, matching gender, age, geographical area of residence and diagnosis. Fig 1 shows the SPIRIT 2013 schedule of enrollment, interventions, and assessments. Fig 2 includes a flow chart of the main parts of the study methods.

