**Fig 2 pone.0274193.g002:**
[figure not shown]
Study methods flow chart. 134 participants will be assessed for elegibility, allocating 67 in each arm (experimental and control groups). COT-MHABI protocol will be applied in experimental group and regular health care interventions in control group. For both groups, outcomes will be assessed over a one-year period at baseline, by the 6^th^ and 12^th^ month, when data collection is closed and analysis begins.

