### Statistical analysis

Data will be analysed on an intention-to-treat basis [61] i.e. results will be analysed using the basis of all participants. For missing data, the multiple imputation method will be used.

All variables will first be checked for normality. To test the effectiveness of the intervention, continuous variables having normal distribution will be analysed by repeated measures analysis of variance, ANOVA (within-subject factors: baseline, intermediate evaluation, final evaluation), comparing the two groups (between-group factors).

Due to the proposed design and the technical feasibility of the experimental group provider site, non-simultaneous recruitment makes the potential exposure to certain external factors unequal for some subjects. These factors may include the season of the year or the phase corresponding to the COVID-19 pandemic situation. To control them, we will explore the differences in the proportion of participants for these variables between the two groups using chi-square tests. If there are differences between groups an ANCOVA will be carry out with these external factors as covariates.

Non-normally distributed variables will be analysed using the Mann-Whitney test for group comparison. Friedman analyses and the Wilcoxon signed-rank test will be used for intrasubject factors. A p value < .05 will be defined as statistically significant. Bonferroni correction will be carried out for planned comparisons.

To determine the contribution of satisfaction with activities on quality of life in people with brain injury and a diagnosis of mental illness, beyond the intervention performed, a hierarchical regression analysis will be performed with the entire sample, including the following variables in model 1: belonging to the intervention group, age and level of functionality. In model 2, in addition to the variables in model 1, the variable satisfaction with the occupation (collected by SDO-OB) will be added.

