### Limitations

Due to the technical feasibility of the programme, where the intervention is carried out, the clinical and social complexity of this patient profile, the lack of evidence on similar programmes and interventions, and the difficulties in finding a population in the setting that falls within the range of the inclusion and exclusion criteria, the presence of these issues that may interfere with the results and lead to bias should be highlighted.

The following have been identified as the main ones: (i) the inclusion of various aetiologies of ABI as a generalised concept, when the clinics presented by the patients may differ considerably [62]; (ii) the difficulty of knowing the influence of the different treatments that the patients in the control group may receive; (iii) the variability in the different conceptions of the construct "mental health" and its implications in the design of the protocol itself as well as in the practice on the quality of professional support that this population profile receives; (iv) due to the technical particularities of the research proposal, the therapist delivering the intervention and subsequently analysing a large part of the data is the same person, which may lead to biases in the results; (v) the heterogeneity in terms of the range of time after ABI in which the intervention takes place, as both groups have a wide range. This is because, at present, this is the first time that this type of support initiative is being provided in this region; so, patients are not screened according to the time of acquisition of the brain injury but by the importance of the current condition and their personal, occupational, social, and family issues.

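### Limited places and a waiting list restrict how many patients can start COT-MHABI, not which ones, so the stated reason does not by itself rule out random allocation

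*Protocol article*

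**What the plan says.** Under Trial design and setting, the protocol article gives one sentence of justification: "Due to the logistical reasons discussed above, a non-randomised controlled clinical trial will be performed". The reasons it points back to are in Recruitment methods, where "the resources for its implementation are limited, generating a waiting list (over 12 months" describes the constraint. That section then turns the wait into the control condition. It begins "Given that this standby period is longer than the duration of the intervention in the experimental group" and concludes that "patients on the waiting list will be invited to participate in the control group with the consideration of receiving the intervention at a later stage".

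Other features of the design bear on whether a draw would be possible:

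- **Source of patients.** "For both the experimental and control groups, the referral of patients to the study will take place through the neuropsychiatry department". That department takes no part in allocation.
- **Eligibility and follow-up.** Both groups have the same criteria and are assessed at baseline, 6 and 12 months, with 67 patients per arm (Fig 2 caption).
- **Control of confounding by design.** Trial design and setting names matching on gender, age, area of residence and diagnosis.
- **Control of confounding by analysis.** Statistical analysis acknowledges that "non-simultaneous recruitment makes the potential exposure to certain external factors unequal for some subjects", giving season and pandemic phase as examples. It plans an ANCOVA on these factors only if chi-square tests show a difference between groups.

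No section says how it is decided which patient gets a place and which one waits. The five main limitations that the article lists do not include non-random allocation.

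**The concern.** The first objective is to evaluate effectiveness, and the Discussion would read significant results as a step towards confirming that the intervention raises quality of life. That reading requires the arms to be comparable apart from treatment.

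Scarcity fixes the number of starters. It does not fix their identity, and identity is what random allocation governs. Without a draw and without a stated rule, patients who start and patients who wait may differ in time since injury, in calendar period and in prognostic features that nobody records. Those differences then become part of the estimated effect. Adjustment can remove only what has been measured and modelled.

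**Working it through.** **1. Does the stated reason exclude a draw?** The article's own description can be set against what a randomised waiting-list design needs.

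| Requirement | What the article describes |
|---|---|
| More eligible patients than places | Limited resources and a waiting list |
| Wait at least as long as follow-up | Wait of over 12 months; last assessment at 12 months |
| Controls treated later | Yes |
| Common source and criteria | One referring department, one set of criteria |
| Same assessments in both arms | Baseline, 6 and 12 months |

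Every requirement is met, and nothing in the stated reason conflicts with a draw.

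**2. Does a draw need more patients or places?** Power analysis and sample size calculations gives d = 0.49, two-sided alpha 0.05, power 0.80 and a total of 134. The exact two-sample t calculation gives 66.35 per arm, rounded up to 67. The total is 2 × 67 = 134, with power 0.804, so the stated figure reproduces. A 1:1 draw uses the same calculation: 134 patients, 67 of them starting at once.

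**3. What do the planned safeguards leave open?** Matching covers four variables. Time since injury, severity, the NPI-Q and the baseline outcome are not among them. The ANCOVA covers only season and pandemic phase, and only when a chi-square test flags a difference. Unmeasured prognosis is covered by neither.

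**4. How much could a residual difference matter?** The documents give no figure, so this step rests on assumption. Let b be a residual difference between arms in SD units. For a two-sample t-test with 67 per arm (132 degrees of freedom), the noncentrality is b × √(67/2) = b × 5.788. With no true effect, the two-sided rejection probability is the chance that a noncentral t falls outside the 2.5% and 97.5% points of the central t. If the true effect is 0.49 and b works against the intervention, the noncentrality is (0.49 − b) × 5.788.

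| Assumed b (SD) | b ÷ 0.49 | Noncentrality, no true effect | False-positive rate | Power if b opposes a true 0.49 |
|---|---|---|---|---|
| 0 | 0% | 0 | 5% | 80% |
| 0.1 | 20% | 0.579 | 8.9% | 61% |
| 0.2 | 41% | 1.158 | 21.0% | 38% |
| 0.3 | 61% | 1.736 | 40.7% | 19% |

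This uses the simple two-group test behind the sample size, not the planned repeated measures ANOVA. It shows sensitivity to bias and does not estimate the bias in this trial.

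**The case against.** The design is openly called non-randomised. The arms share a referral source, criteria and visits, they are matched on four factors, and two calendar factors may be adjusted for. Controls are followed during a wait they would have had anyway. Under a draw, a patient whose turn has come could instead be assigned to wait. That is a real cost to patients and may affect consent and retention. The Limitations also report difficulty in finding eligible patients, so exact matched pairs available whenever a place opens may not be achievable. All of this stands, and it shapes the fix. None of it shows that scarcity prevents a draw.

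Four stronger readings are tempting but not supported:

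- **That clinical need decides the arm.** A reader might infer this from the Limitations, where "patients are not screened according to the time of acquisition of the brain injury but by the importance of the current condition". That sentence explains why time since injury varies widely in both groups. It describes screening into the programme and says nothing about who starts and who waits.
- **That the plan already forms pairs.** The matching sentence fits group-level matching equally well.
- **That randomisation was given up without any need.** Statistical analysis also mentions the technical feasibility of the provider site, and the article condenses a fuller protocol that may give further reasons. What can be said is that the reason stated here is not sufficient.
- **That a draw would give an unbiased answer.** The two main outcomes are self-reported, and the Intervention section has the treating therapist evaluate the experimental group. Randomisation would not remove bias from either.

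The direction of bias is also unknown. If treated patients have already waited longer, recovery during follow-up could favour the controls, and the loss would be in power.

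**Conclusion.** The point holds in limited form, as an improvement that should be made. Limited places and a long list do not by themselves justify leaving allocation to an unstated process. Non-simultaneous recruitment is conceded, and the planned matching and conditional ANCOVA address only part of what may differ between arms. A 1:1 draw leaves the requirement at 134 patients and 67 places.

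The consequence cannot be sized from the documents. Under assumed shifts of 0.1 to 0.3 SD, the false-positive rate would be about 9% to 41% in place of 5%, or power about 61% to 19% in place of 80%, depending on direction. The conclusion rests on the article's stated reason. A further obstacle in the full protocol could change whether a draw is feasible, but it should then be given as the reason.

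**What to change.** Amend Recruitment methods and Trial design and setting as follows:

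- As places open, randomise consenting eligible patients in small time blocks to immediate start or to the existing wait as control. Stratify on a few of the matching factors where feasible; exact pairs are not required.
- Have the sequence held by someone outside treatment and assessment. The hospital research department also stores the data and audits the study, so giving it the sequence would mean that it audits its own allocation.
- Take baselines of both arms in the same period, so that season and pandemic phase are balanced by design.
- Fill any places that must go by need outside the trial, and report participants already allocated separately as non-randomised.

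**Cost.** An ethics amendment and a random list; the programme loses its choice over starting order; some patients wait longer than list order would give. The number of places, patients, visits and staff does not change.

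**If a draw truly cannot be done.** State the actual obstacle and the rule that decides who starts, and enrol controls concurrently with treated patients. Plan adjustment for baseline outcome, severity, NPI-Q and time since injury whatever the result of a preliminary test. List selection bias as a limitation and restrict the effectiveness conclusion accordingly.

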#### Power analysis and sample size calculations

Theoretically, with a two-tailed test, a sample of 134 participants will be needed in order to detect a significant difference in WHOQoL-BREF showing an effect size d = 0.49 (alpha = 0.05, beta = 0.20, power = 0.80), according to data collected in Chiu et al. (2016) [47]. The sample was calculated using the GPower 3.1 program.

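### The arms are matched on gender, age, area and diagnosis, but no effectiveness analysis includes these factors, so residual imbalance goes uncorrected and precision is lost (minor; the 134 is not too small on this ground)

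*Protocol article*

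**What the plan says.** **Design.** The Protocol article, under Trial design and setting, describes a non-randomised controlled trial and states: "The measurement points of both groups will be comparable, matching gender, age, geographical area of residence and diagnosis". It does not say whether this means individual pairs or similar group frequencies. Recruitment methods says that controls are patients on the waiting list who are invited to take part. The Fig 2 caption adds: "134 participants will be assessed for elegibility, allocating 67 in each arm (experimental and control groups".

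**Sample size.** Power analysis and sample size calculations reads: "Theoretically, with a two-tailed test, a sample of 134 participants will be needed", with "effect size d = 0.49 (alpha = 0.05, beta = 0.20, power = 0.80". No matching or correlation enters.

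**Analysis.** Under Statistical analysis, normally distributed variables get "repeated measures analysis of variance, ANOVA (within-subject factors: baseline, intermediate evaluation, final evaluation), comparing the two groups (between-group factors". For the rest: "Non-normally distributed variables will be analysed using the Mann-Whitney test for group comparison". The Friedman and Wilcoxon signed-rank tests are for change within a subject, not for matched arms. An ANCOVA follows only if chi-square tests show that the groups differ on external factors, with season and pandemic phase as the examples. Age appears only in the hierarchical regression of quality of life on satisfaction with occupation. Gender, area and diagnosis appear in no model.

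**The concern.** In a non-randomised comparison, matching is the main stated protection against differences between the patients in the two arms. It is seldom exact. The Fig 2 caption, as written, has 134 people assessed and all 134 allocated, which leaves no surplus from which to choose close matches. The Limitations section says that eligible patients are hard to find and that aetiologies vary. Some imbalance in the four factors is therefore plausible, and the plan has no step that would correct it.

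Two things are at stake. The estimated effect carries whatever imbalance remains, to the extent that the factors predict the outcome analysed. The analysis also forgoes the precision that these factors could give. If individual pairs are formed, a further question is whether a standard error and a power figure for independent groups fit the design.

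**Working it through.** **1. The plan's own figure.** Inputs from the sample size section: d = 0.49, two-sided alpha 0.05, power 0.80. For an independent two-sample t test with 67 per arm, the noncentrality is 0.49 × √(67/2) = 2.836 on 132 degrees of freedom, with critical value 1.978. Exact power is 0.804; with 66 per arm it is 0.798. So 134 is reproduced exactly as an unmatched calculation.

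**2. Are the matching factors in any effectiveness test?**

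| Analysis | Gender, age, area, diagnosis | Pair term |
|---|---|---|
| Repeated measures ANOVA | none | no |
| Mann-Whitney | none | no |
| Conditional ANCOVA | none (external factors only) | no |
| Hierarchical regression (not an effectiveness test) | age only | no |

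**3. What residual imbalance does.** At one time point, the bias from a factor is its slope on the outcome times the difference between arms in its mean. For change from baseline, it is the difference between the slopes at follow-up and baseline times the same imbalance. The documents give neither slopes nor expected imbalance, so no size can be attached. A factor that affects only the level of the outcome drops out of change. One that affects recovery does not.

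**4. Standard error if individual pairs are formed.** Let r be the within-pair correlation of the outcome. It is not in the documents, so 0 to 0.3 is an assumption. For a single-time-point comparison:

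- nominal/true standard error = 1/√(1 − r)
- real alpha = 2 × [1 − Φ(1.96/√(1 − r))]
- power of the planned unpaired test ≈ Φ((2.836 − 1.978)/√(1 − r))
- power of a paired analysis: noncentral t with 67 pairs and standardised difference 0.49/√(2(1 − r))

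| r | SE too large by | Real alpha | Power, planned test | Power, paired |
|---|---|---|---|---|
| 0 | 0% | 0.050 | 0.80 | 0.80 |
| 0.1 | 5% | 0.039 | 0.82 | 0.84 |
| 0.2 | 12% | 0.028 | 0.83 | 0.88 |
| 0.3 | 20% | 0.019 | 0.85 | 0.92 |

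With 1.978 in place of 1.96, alpha for r = 0.1, 0.2 and 0.3 is 0.037, 0.027 and 0.018.

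**5. Does this carry over to change from baseline?** This was simulated with 67 pairs, a pair effect that is stable over time, an assumed within-subject correlation of 0.6 and 10,000 replicates. For r = 0, 0.1 and 0.3:

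| Unpaired comparison | Alpha | Power at 0.49 |
|---|---|---|
| Change from baseline | 0.049, 0.049, 0.052 | 0.88, 0.88, 0.88 |
| Final value only | 0.050, 0.037, 0.018 | 0.80, 0.82, 0.84 |

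The misfit appears in the single-time-point comparison and all but vanishes for change.

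**The case against.** A reader might infer that the standard errors, p values and power of the trial do not fit its design. The documents do not support that, for four reasons.

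- **Pairs are never established.** The sentence on matching gives no pair, ratio or tolerance, and its subject is the measurement points of the groups. Group-level matching fits the text as well, and the figures in step 4 do not apply to it.
- **Any error is conservative.** Alpha falls below 0.05 and power stays at or above 0.80. Matching creates no extra false-positive risk and does not leave the trial too small.
- **The main planned contrast is hardly touched.** In the repeated measures ANOVA, effectiveness is shown by group-by-time, where a stable matching effect cancels. COPM, a main outcome, is itself scored as change.
- **The correlation is assumed and may be near zero.** Eligibility already restricts age to 18–50, residence to one province and injury to medium or severe.

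All four stand, and they reduce the standard-error argument to a side issue. They do not remove the point about adjustment. Cancellation requires that the factors affect level but not recovery, and the Mann-Whitney test is named for group comparison without specifying a change score.

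It can also be said that a condensed article leaves detail to the full protocol or analysis plan. That is fair for the matching procedure, whose absence here is no finding. It does not cover the tests and the covariate rule, which the article states and which leave these factors out.

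**Conclusion.** The point holds as a minor one. The article matches two non-randomised arms on four factors, then fixes effectiveness analyses that use none of them and a covariate rule limited to external factors. Residual imbalance is uncorrected and precision is lost. Neither can be sized from the documents.

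The effect on the standard error is conditional. It needs individual pairs, factors that predict outcome, and a single-time-point comparison. Over the assumed correlations of 0 to 0.3, the standard error is then 0% to 20% too large, alpha is 0.05 to 0.019 and power is 0.80 to 0.85. The statement that "a sample of 134 participants will be needed in order to detect a significant difference in WHOQoL-BREF" is sound for independent groups and, on this ground, errs on the safe side.

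**What to change.** - Include gender, age, area of residence and diagnosis as prespecified covariates in the effectiveness model for every outcome, regardless of any baseline test.
- Include their interactions with time. A covariate entered only as a main effect shifts all visits equally and does not bear on group-by-time.
- For non-normal outcomes, replace the unadjusted Mann-Whitney test with a covariate-adjusted method, for example rank ANCOVA or the same model with robust or bootstrap standard errors.
- If individual pairs are formed, add a pair term. Keep 134 and describe it as an unmatched, conservative calculation.

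**Cost.** This changes analysis wording only. The four factors must already be known for each patient if they are used for matching, and no further patients are needed. The price is a few degrees of freedom, so sparse categories of area and diagnosis should be collapsed, by a rule set in advance.
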